#### Electroencephalography

EEG is a useful tool for inhibitory network assessment. This study aims to understand better the effects of inhibitory networks on the rehabilitation process. Successful inhibition is associated with increased EEG power in theta and delta bands (51, 52). Thus, we hypothesize that a better functional state will be related to the increase in power in the EEG delta and theta bands in the resting state, as well-modifications of others EEG bands (alpha, beta, and gamma).

We will use the same methodology of our other trial also looking at the inhibitory activity using EEG (53). EEG will take place over ~45 min: 25 min of participant and software preparation, 10 min of EEG recording divided into a resting EEG condition (5 min with eyes open and 5 min with eyes closed), and a task-related condition (8 min). Participants will be asked to relax in the resting condition; the investigator will ensure they do not fall asleep.

The task-related condition will include movement observation, movement imagery, and movement execution. This will be recorded by connecting the Net Station software (for EGI) with E-Prime. The entire task-related condition part will consist of 60 trials, with 20 trials for each of movement observation, movement imagery, and movement execution in a randomized order.

We will record the EEG in a standardized way using the 64-channel EGI system (EGI, Eugene, USA). The EEG will be recorded with a band-pass filter of 0.3–200 Hz and digitized at the sampling rate of 250 Hz by connecting the Net Station software (for EGI) with E-Prime.

#### Electroencephalography Data Assessment

The EEG data will initially be analyzed visually by a specialist clinical neurophysiologist who will identify and signal the artifacts, in addition to possible clinical changes in the EEG. Then, the data will be exported and analyzed offline with EEGLab (54) and MATLAB (MATLAB R2014b, The MathWorks Inc. Natick, MA, 2000). The following standard bands and frequencies will be analyzed: delta (2–4 Hz), theta (4–8 Hz), alpha 1 (8–10.5 Hz), alpha 2 (10.5–13 Hz), beta 1 (13–20 Hz), and beta 2 (20–30 Hz). Sensory inhibition will also be analyzed through the methods already described in this protocol.

Furthermore, a coherence analysis will be carried out through the MATLAB “mscohere” function, which calculates the estimate of coherence squared of magnitude, which is a function of power spectral density and the cross power spectral density of two channels. A coherence value between 0 and 1 will be calculated for each frequency point for the selected channel pairs. High coherence between two EEG signals has been considered as evidence of the possible existence of a structural and functional connection between two cortical areas.

Initially, only the electroencephalographic activities related to the primary motor cortex (CZ, C3, and C4) will be used for multivariate regression models, in addition to transversal inter-hemispheric coherence (C3–C4) and front-central intra-hemispheric coherence, F3–C3, and F4–C4. The data referring to the other EEG channels will be stored for future exploratory analyzes.

#### Functional Near-Infrared Spectroscopy

The relative changes in the concentration of oxy- and deoxyhemoglobin will be evaluated for each condition (left-hand grip, right-hand grip, and both hands grip), including rest (interval between each activity block). An average of the 10 trials will be made for each condition to improve the signal-to-noise ratio. A correlation analysis (seed-based correlation analysis) will also be carried out, estimating the strength of the neural connections related to the channels positioned on the M1 brain area, which can help elucidate the null hypothesis.

#### Functional Near-Infrared Spectroscopy + Electroencephalography Recording Protocol

EEG recording will be carried out concurrently with fNIRS. There will be 10 min of recording at rest (the first 5 min with the eyes closed and the last 5 min with the eyes open). Then, the patient will be asked to open and close his hands at a frequency of 1 Hz, using a video to guide the frequency of their movements. For fNIRS, the patient will be asked to open and close his hands at a frequency of 1 Hz, using a video to guide the frequency of their movements. There will be five 30-s blocks in which the patient will execute right-hand movements and five 30-s blocks imagining the right-hand movements, with an interval of 30 s between blocks. The same protocol will be repeated for the left hand and with simultaneous movements of both hands resulting in a total fNIRS collection time of ~30 min.

#### Magnetic Resonance Imaging

Diffusion tensor imaging with fractional anisotropy (FA) will be used to collect the MRIs. The regions of interest will be the bilateral primary motor cortices and fibers of the corpus callosum and corticospinal tract. After obtaining the diffusion tensor imaging data, FA values will be determined for all corpus callosum and corticospinal fibers. The FA value of 0.15 will be considered as a reliable threshold to isolate the white matter from the rest of the brain (55). The volumetric measurement of the motor cortex will also be taken.

Initially, only the primary motor cortex thickness will be used for the analysis. We will select 10% of the sample, resulting in a total of 40 patients. These results will be analyzed with multivariate models, including only these patients in a subgroup analysis.

### Statistical Analysis

For this analysis, we will use the multivariate regression model in which motor improvement will be the dependent variable and changes in inhibitory activity (resulting from neurophysiological assessments performed before and after treatment) will be the independent variables.

To control the impact of different conditions on the multivariate model, we will create a “dummy variable” for each disease etiology. Moreover, demographic characteristics (age, education, sex, and ethnicity) and clinically relevant characteristics (duration of illness, comorbidities, and the use of medications) will be tested, as well as specific aspects for each disease, such as the stroke side, the level of spinal cord injury, the degree of bone deformity of knee OA, and the level of lower limb amputation. The neurophysiological biomarkers described earlier will be tested in the same model.

Although this study's aim is not to test interventions but to identify changes in biomarkers related to functional improvement (regardless of the therapy performed), the different therapies performed by patients will be quantified, including information such as the number of sessions, frequency, duration, among others, which can be used in future analyses.

For secondary analyzes, functional improvement can be assessed by the several, general and specific, scales used depending on the evaluated disease. In this situation, we will use the calculation of the functional modification's effect size and not the absolute values of the scale for the analysis in the multivariate model.

Also, the motor function of the upper limb will only be assessed for patients with stroke and spinal cord injury, the main scale used being the Fugl–Meyer Assessment. In this case, an analysis similar to the one described earlier will be performed but only including these two populations.

Some of the scales, such as those for mood, pain, cognition, and sleep, will be used to characterize the sample, in addition to possibly being used to control confounders in the multivariate model. Besides, mood, pain, and cognitive disorder are commonly present in these populations, so we will perform an exploratory analysis using a similar statistic method but with scales related to these aspects as dependent variables.

In the statistical analysis for the results of the obtained polymorphisms, classical methods of case–control studies' epidemiological analysis will be applied. Odds ratio and the respective 95% confidence intervals will be estimated by unconditional logistic regression to simultaneously control potential confounding variables. To assess the relationship between the dependent variable (stroke and its subtypes) and the independent variables (polymorphisms of the evaluated genes, smoking, lipid variables, etc.), the statistical technique used will be logistic regression analysis, which allows the evaluation of disease risk associated with a given variable considering all other independent variables in the model.

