## Abstract

**Background:** Brain plasticity is an intrinsic property of the nervous system, which is modified during its lifetime. This is one mechanism of recuperation after injuries with an important role in rehabilitation. Evidence suggests that injuries in the nervous system disturb the stability between inhibition and excitability essential for the recuperation process of neuroplasticity. However, the mechanisms involved in this balance are not completely understood and, besides the advancement in the field, the knowledge has had a low impact on the rehabilitation practice. Therefore, the understanding of the relationship between biomarkers and functional disability may help to optimize and individualize treatments and build consistent studies in the future.

**Methods:** This cohort study, the deficit of inhibition as a marker of neuroplasticity study, will follow four groups (stroke, spinal cord injury, limb amputation, and osteoarthritis) to understand the neuroplasticity mechanisms involved in motor rehabilitation. We will recruit 500 subjects (including 100 age- and sex-matched controls). A battery of neurophysiological assessments, transcranial magnetic stimulation, electroencephalography, functional near-infrared spectroscopy, and magnetic resonance imaging, is going to be used to assess plasticity on the motor cortex before and after rehabilitation. One of the main hypotheses in this cohort is that the level of intracortical inhibition is related to functional deficits. We expect to develop a better understanding of the neuroplasticity mechanisms involved in the rehabilitation, and we expect to build neurophysiological “transdiagnostic” biomarkers, especially the markers of inhibition, which will have great relevance in the scientific and therapeutic improvement in rehabilitation. The relationship between neurophysiological and clinical outcomes will be analyzed using linear and logistic regression models.

**Discussion:** By evaluating the reliability of electroencephalography, functional near-infrared spectroscopy, transcranial magnetic stimulation, and magnetic resonance imaging measures as possible biomarkers for neurologic rehabilitation in different neurologic disorders, this study will aid in the understanding of brain plasticity mechanisms in rehabilitation, allowing more effective approaches and screening methods to take place.

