
## Methods and Analysis

### Participants and Study Design

This is a prospective cohort study made up of four groups with a specific diagnosis (stroke, spinal cord injury, knee OA, or lower limb amputation) and a group of healthy volunteers.

Patients admitted to the conventional rehabilitation program of the Instituto de Medicina Física e Reabilitação (IMREA) will be invited to participate in the study and included after signing the informed consent form previously approved by the Hospital das Clínicas da Faculdade de Medicina da Universidade de São Paulo Ethics Committee for Research Protocol Analysis CAAE: 86832518.7.0000.0068. For this study, 400 patients will be recruited, 100 patients with a stroke diagnosis, 100 with knee OA, 100 with spinal cord injury, and 100 amputee patients. The control group will be made up of 100 healthy subjects paired by sex and age.

Patients who agree to participate in the study will undergo a series of assessments at two time points: before and after the IMREA rehabilitation program. An individualized approach characterizes this program, considering the injury's etiology, the type of disabilities the patient has, general clinical conditions, likely prognosis, and the patient's socioeconomic factors. The control group will only perform neurophysiological (EEG, fNIRS, and TMS) and functional assessments once.

It is important to note that all patients involved in the research will receive the same type of treatment as patients who are not participating in the research.

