In this context, TMS is a widely used tool to measure corticomotor excitability in patients with motor deficit conditions such as stroke. It has been found that motor deficit severity is highly associated with the level of corticomotor excitability measured by rMT depicted in TMS results. Given that rMT reflects neuronal membrane excitability, functional modifications that occur after motor deficit conditions, such as inhibitory circuit malfunctions, are reflected as rMT alterations in TMS (68). We expect to find a reduction in inhibitory brain activity associated with a decrease in rMT, SICI, and SP due to the direct relationship between these biomarkers and motor inhibitory pathways of the brain. Moreover, study findings show that ICF and MEP are mediated by different interneuronal pathways than those of rMT, SICI, and SP; thus, it is expected that as inhibitory circuits increase their activities, ICF and MEP amplitudes will be decreased (69).

Several studies have conveyed brain plasticity alterations in the primary motor cortex. These changes have been thus identified through the use of biomarkers such as EEG and fNIRS, for instance, strong correlations between theta and delta band activities in the hippocampus and successful inhibitory mechanisms in rodent models (70). The use of EEG as a biomarker “tracker” thus becomes important because sensory inhibition reflects an automatic cortical inhibition function, which can be used as a measure of the brain's inhibitory status (71–74). These findings support one of the study's main hypotheses that motor function deficits are associated with lower cerebral inhibitory activity when compared with a healthy control group. Studies that have performed electrophysiological evaluations of patients with chronic pain conditions such as OA, spinal cord injury, and neurogenic pain have found a decrease in theta and delta wave activity and an increase in beta wave activity due to deficient brain inhibitory circuits (75). Thus, an increase in the activity of theta and delta bands, as well as a decrease in beta bands, is a reflection of increased inhibitory activity, which can be achieved through rehabilitation in patients with pain conditions. Therefore, given these findings, we expect a diminished event-related desynchronization in patients with motor dysfunctions.

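### Two main hypotheses concern the level of inhibition, but the only model stated for inhibition and function regresses change on change and cannot include the 100 controls

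*Protocol article*

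**What the plan says.** **Hypotheses.** The Abstract states: "One of the main hypotheses in this cohort is that the level of intracortical inhibition is related to functional deficits". The Discussion gives, again as one of the main hypotheses, that "motor function deficits are associated with lower cerebral inhibitory activity when compared with a healthy control group". Both are statements about levels.

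**Model.** The regression is set out in Statistical Analysis: "motor improvement will be the dependent variable and changes in inhibitory activity". The latter, taken from the two assessments of each patient, are the predictors. For the grouping of participants, "we will create a “dummy variable” for each disease etiology"; no term for patient versus control is given. The secondary analyses also take functional change as the outcome, expressed as an effect size. The upper-limb analysis (stroke and spinal cord injury only) and the exploratory analyses of mood, pain and cognition are described as similar in form.

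**Participants.** Under Participants and Study Design, "400 patients will be recruited, 100 patients with a stroke diagnosis, 100 with knee OA, 100 with spinal cord injury, and 100 amputee patients", and these patients are assessed before and after rehabilitation. The same section describes the comparison group: "The control group will be made up of 100 healthy subjects paired by sex and age". On the timing of its measurements, it adds: "The control group will only perform neurophysiological (EEG, fNIRS, and TMS) and functional assessments once".

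**The concern.** The hypotheses and the model address different quantities. Whether disabled patients have less inhibition, and whether those with less inhibition function worse, are cross-sectional questions about levels. Whether motor improvement goes with change in inhibition is a longitudinal question. A patient can have low inhibition and poor function at baseline whatever the relation between later changes.

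The control group makes the mismatch concrete. Its evident purpose is the healthy reference in the Discussion's hypothesis, yet the stated model has no place for it.

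If only the stated model were run, a null result would not show that inhibition is normal in disability, and a positive one would not show that it is reduced. A level analysis added after the data are seen would be exploratory, with many candidate markers from TMS, EEG and fNIRS to choose from.

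**Working it through.** **1. The plan's own figure.** Sample Size gives 100 per condition, 10 covariates and an effect size of about 0.3, without alpha, power or the effect-size metric, so it cannot be strictly reproduced. It fits a rule of 10 subjects per covariate (100/10). If 0.3 is a correlation, at two-sided 5%:

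- n = ((1.960 + 0.842)/atanh 0.3)² + 3 = (2.802/0.3095)² + 3 ≈ 85 for 80% power, and 113 for 90%.
- n = 100 gives 86% power. As a partial correlation with 10 covariates it gives 88%; as an overall f² of 0.3 it gives 97%.

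None of these readings involves the controls.

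**2. Hypotheses against the stated model.**

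| Question | Outcome and predictor needed | In the stated model? |
|---|---|---|
| Level related to deficit | Baseline function; baseline inhibition | No: both are changes |
| Lower than in controls | Baseline inhibition; patient or control status | No: controls have no change and no group term |
| Change related to recovery | Improvement; change in inhibition | Yes |

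**3. Can the change model stand in for a level test?** A simulation of 2,000 runs per scenario used 400 patients and 100 controls, with changes generated independently of baseline levels.

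| True state | Change model rejects | Level test rejects | Patient-control test rejects |
|---|---|---|---|
| Level r = 0.3, control difference d = 0.4, change r = 0 | 5.0% | 100% | 94% |
| Level r = 0, d = 0, change r = 0.3 | 100% | 4.8% | 5.3% |

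The independence is built in, so this illustrates the logic and does not forecast the trial's data. It shows that the level hypotheses can be true while the change model rejects only at its type I error rate, and the reverse.

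**4. What the planned numbers could detect at baseline.** Two-sided 5% and 80% power are assumed.

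- 400 patients versus 100 controls: d = 2.802 × √(1/400 + 1/100) = 2.802 × 0.1118 = 0.31. Power at d = 0.3 is 77%.
- One condition versus controls: d = 2.802 × √(1/100 + 1/100) = 2.802 × 0.1414 = 0.40. Power at d = 0.3 is 56%.
- The same contrast made for four conditions with Bonferroni (0.05/4 = 0.0125): d = (2.498 + 0.842) × 0.1414 = 0.47.
- Level on deficit, 400 patients: r = tanh(2.802/√397) = 0.14. A partial correlation with 10 covariates gives the same to two decimals. With 100 patients and 10 covariates the partial r is 0.27.

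These are before missing data and before any gain in precision from age and sex.

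**The case against.** The strongest reply is that this is a journal article: a baseline comparison of patients with controls, or a cross-sectional regression, is the sort of detail that a full protocol or SAP supplies. That stands against any claim that the hypotheses will go untested. A reader might infer that the study must finish without such a test; the article cannot show that. It does not answer the narrower point, because the article fixes an outcome and predictors for inhibition and function, and these do not match hypotheses that it calls main ones.

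Second, the article is not silent on levels. The Abstract says that neurophysiological and clinical outcomes will be related by linear and logistic regression, and the Introduction describes baseline assessments to be correlated with functional deficits. That shows intent for the first hypothesis, but neither place gives a model of deficit on level or a contrast with controls. Statistical Analysis also says that the biomarkers will be tested in the same model. Even if that admits baseline values as predictors, the outcome is still improvement and controls still drop out.

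Third, the change model is a sound match for another aim stated in Statistical Analysis, to identify biomarker changes that accompany functional improvement. This is correct. The gap affects two hypotheses among several, not the whole study.

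Two further inferences are tempting and fail. One is that the controls are used nowhere: the logistic analysis of polymorphisms may use them as non-cases, although it names neither inhibition nor function. The other is that 100 controls cannot be paired with 400 patients. The article does not say to whom they are paired or whether pairing is individual, and it gives no age or sex distributions; one control could in principle serve one patient from each condition.

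**Conclusion.** The point holds as a mismatch between stated hypotheses and stated model. Two hypotheses about the level of inhibition have no stated analysis, and 100 of 500 participants (20%) enter no stated neurophysiological analysis. This rests on the article's text, not on a power calculation.

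The numbers show only that the gap can be closed with the planned sample. The pooled contrast is reasonably sensitive and the level-on-deficit regression highly so; single-condition contrasts are weaker, especially once adjusted for four comparisons. Because all the baseline measurements needed are already scheduled for patients and controls, nothing is lost if the analyses are specified before the data are examined.

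**What to change.** Add two analyses to Statistical Analysis, named as the tests of these hypotheses.

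- **Patients versus controls.** Regress baseline inhibition on patient or control status, with age and sex in the model. Use SICI, the measure of intracortical inhibition under Transcranial Magnetic Stimulation, as the lead marker and treat the others as secondary. Pool the four conditions first, since Sample Size seeks alterations that they share. Make per-condition contrasts secondary and adjust them for multiplicity.
- **Level and deficit.** In patients, regress baseline function on baseline inhibition, adjusted for etiology, age, sex and duration of illness. Prespecify one functional measure that Table 1 lists for all four conditions, for example the Functional Independence Measure or a gait test. The Fugl–Meyer Assessment would not serve, as it covers only stroke and spinal cord injury.

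Keep the change-on-change model for the recovery aim, and say which analysis is primary. Keeping age and sex in the control comparison is enough; the description of the pairing need not change on this account.

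The cost is wording and two extra models on data already scheduled, with no new participants, visits or procedures.

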### Sample Size

The sample size of 100 patients for each type of injury was determined, given this is an observational study (prospective cohort) and, thus, the primary analysis being a linear regression. Therefore, 100 participants in each group will allow for the modeling of 10 covariates, which will yield an effect size of ~0.3, which we believe is enough, mainly due to the use of neurophysiological variables and our knowledge of previous studies. Our group recently performed two studies with multivariate analyses, one with 35 and another with 55 patients, to assess neurophysiological markers (EEG and TMS), which allowed us to identify the role of these markers in the rehabilitation of conditions such as stroke.

Thus, using a larger sample (100 subjects), compared with our previous studies, associated with a larger detailing of clinical and neurophysiological information, will aid in the better comprehension of cerebral plasticity. We also believe this sample size will yield similar results for patients with knee OA, spinal cord injury, and amputation. Furthermore, it will allow for the identification of transdiagnostic markers, not aiming to compare the different injury groups but to determine the neurophysiological alterations they have in common.

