### Neurophysiological Assessment Methods

#### Transcranial Magnetic Stimulation

The Magstim Rapid® stimulator (The Magstim Company Limited, United Kingdom) and a 70-mm coil in figure-of-eight will be used, positioned tangentially to the skull and at an angle of 45° in relation to the sagittal line will be used. The muscular response to the stimulus applied to the motor cortex will be recorded using surface electromyography with Ag/AgCl electrodes positioned on the target muscle and the grounding electrode positioned on the wrist. We will follow the methods established in the literature for physiological and clinical studies (50).

Bilateral upper limb assessment (first dorsal interosseous muscle of the hand) will be performed. The motor area corresponding to the first dorsal interosseous is the most used motor cortical area in cortical excitability studies in addition to presenting a greater accuracy of the method due to the local anatomy and penetration of the TMS pulse. To locate the cortical area of the hand, it will initially be identified from the vertex (intersection between the nasion–inion lines and zygomatic arches). Then, for the identification of the probable hot spot, a mark will be made 5 cm from the vertex toward the ear tragus in the coronal plane. The hot spot will be defined as the location as the lowest resting motor threshold and with the greatest amplitude of the motor evoked potential in the target muscle for a given intensity of the upper threshold stimulus.

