This is a novel and feasible observational study that will help the understanding, improvement, and development of the rehabilitation field and allows for the identification of several biomarkers at once, providing further insight for clinical practice in rehabilitation. Furthermore, this study was designed to answer our hypothesis in an optimized way, with a rigorous methodology. Besides that, one of the limitations is that our results will not provide a causal relationship between neurophysiological markers and functional and clinical outcomes. Also, the study may be underpowered, as there are four groups of intervention; to minimize that, we performed a sample size calculation based on the expected effect size regarding previous studies; the neurophysiological surrogate variables are something that could help to address this limitation also. The differences between severities of conditions could lead to different dropout rates in one of the more severe group conditions; this may unbalance the groups' size. Another limitation is that the variability of the clinical phenotypes of the conditions approached by this study could generate some noise in our results. To minimize this limitation, we are planning to do a multivariate analysis, which could minimize relevant confounders that may interfere with our results. Finally, our study may lack generalizability, as the study will be performed in only one center.

On the other hand, this is a novel and feasible observational study that, as mentioned before, will help the understanding, improvement, and development of the rehabilitation field.

In conclusion, understanding brain plasticity in the context of rehabilitation allows for more effective approaches and provides screening evaluations of current rehabilitation techniques. The future results of this study will help to better understand brain plasticity and its mechanisms and its reliable representative biomarkers as well. This knowledge will lead to the development of rehabilitation as has occurred in other fields, such as cardiology. In this context, simple questions such as the posology of the treatment will start to be answered when we have markers to measure the functional recovery and feasible and powered studies will be able to be performed in an extensive and consistent manner.

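### Pooled four-condition regression: etiology dummies do not address spread, so ordinary standard errors misstate a marker's significance if marker and residual spread vary together by condition (minor)

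*Protocol article*

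**What the plan says.** Sample Size describes "the primary analysis being a linear regression". Statistical Analysis gives its content: "motor improvement will be the dependent variable and changes in inhibitory activity" are the independent variables, together with demographic and clinical covariates. Condition enters as follows: "To control the impact of different conditions on the multivariate model, we will create a" dummy variable for each etiology. By Participants and Study Design the pooled set is 4 × 100 = 400 patients: "100 patients with a stroke diagnosis, 100 with knee OA, 100 with spinal cord injury, and 100 amputee patients".

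The Discussion concedes that "the variability of the clinical phenotypes of the conditions approached by this study could generate some noise in our results" and offers multivariate adjustment as the remedy. Scaling the outcome to an effect size is stated for the secondary analyses only. The article names no standard-error estimator and gives no SD by condition for any marker or outcome.

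**The concern.** A dummy for each etiology moves the intercept. It does nothing about four conditions having four different residual spreads, and neither does adjustment for further covariates, which is the remedy the Discussion proposes. Ordinary linear-regression standard errors average the residual variance over everyone. For a given marker that average is the wrong one if the patients who carry most information on the slope (those in conditions where the marker varies widely) also have unusually large or unusually small residuals.

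The design makes this possible for some markers. In the TMS section, "Bilateral upper limb assessment (first dorsal interosseous muscle of the hand) will be performed", and the fNIRS task is opening and closing the hands. Upper-limb motor function is assessed as an outcome only in stroke and spinal cord injury. Hand-based markers may therefore change by different amounts in those two conditions than in knee osteoarthritis or lower-limb amputation. This is an inference from the design, not a figure in the article.

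At stake is which markers are called transdiagnostic. The distortion differs from marker to marker and can go in either direction, for a reason unrelated to neuroplasticity. It arises even if the slope is zero in every condition, so it is separate from whether slopes differ by condition.

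**Working it through.** **The plan's own figure.** Sample Size says "100 participants in each group will allow for the modeling of 10 covariates, which will yield an effect size of ~0.3", without naming the metric, alpha or power, so it cannot be reproduced strictly. Assuming two-sided 5% and n = 100 with 10 predictors, the detectable partial correlation is 0.27 at 80% power and 0.31 at 90%, and power at 0.3 is 0.875. The figure is therefore plausible as a partial correlation. The point below does not touch it.

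**Inputs.** From the article: four conditions of 100, one pooled regression, etiology dummies. Assumed, because the article gives none: two-sided 5%, and SD ratios between conditions of 1.25 to 2.

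**Formula.** Let s be the residual SD and t the marker SD within a condition, with equal group sizes. The true variance of the pooled slope is Σ(n s² t²) / (Σ n t²)². The ordinary formula uses mean(s²) / Σ(n t²). Their ratio is

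V = mean(s² t²) / [mean(s²) × mean(t²)],

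so model SE / true SE = 1/√V and the type I error is 2[1 − Φ(1.96/√V)].

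| Pattern | Ratio | V | Model SE / true SE | Type I, formula | Type I, simulated |
|---|---|---|---|---|---|
| Both wider in the same two conditions | 1.25 | 1.721/1.642 = 1.05 | 0.98 | 5.6% | 5.6% |
| | 1.5 | 3.031/2.641 = 1.15 | 0.93 | 6.7% | 6.7% |
| | 2 | 8.5/6.25 = 1.36 | 0.86 | 9.3% | 9.5–9.6% |
| Both wider in the same single condition | 1.5 | 2.016/1.723 = 1.17 | 0.92 | 7.0% | 7.0% |
| | 2 | 4.75/3.06 = 1.55 | 0.80 | 11.6% | 11.9–12.0% |
| Reverse: marker wide where residual is narrow, two against two | 1.5 | 2.25/2.641 = 0.85 | 1.08 | 3.4% | 3.4% |
| | 2 | 4/6.25 = 0.64 | 1.25 | 1.4% | 1.1–1.4% |
| Residual SD doubled in two conditions, marker SD equal | 2 | 2.5/2.5 = 1 | 1.00 | 5.0% | 5.3% |

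**Equal marker spread.** The last row carries the limit of the point. With residual SDs of 1, 1.5, 2 and 3 but equal marker SDs, simulation gives 4.9%, and 5.1% when group sizes fall to 100/90/80/60. Unequal outcome spread alone does no harm.

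**Graded patterns** (n = 400, six further covariates, 8,000 runs):
- Residual and marker SDs both rising from 1 to 2: 7.6%.
- Residual 1 to 3 with marker 1 to 2: 8.2%.
- Residual 1 to 2 with marker 2 to 1: 2.7%.
- Residual 1 to 3 with marker 2 to 1: 1.8%.
- HC3 errors gave 4.2–5.2% in all seven scenarios of this set, which also included equal spreads.

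**Lost power, reverse pattern at ratio 2, slope 0.1.** Here Σ n t² = 400 × 2.5 = 1,000. The true SE is √(400 × 4)/1,000 = 0.040 and the ordinary SE is √(2.5/1,000) = 0.050. The ordinary test needs an estimate above 1.96 × 0.050 = 0.098, so its power is Φ((0.1 − 0.098)/0.040) = Φ(0.05) = 52%. With the correct SE it is Φ(0.1/0.040 − 1.96) = Φ(0.54) = 71%. Simulation with HC3 gives about 68%.

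**The MRI subgroup.** With 4 × 10 patients, equal spreads, six covariates and a slope of 0.5 SD, HC3 has a type I error of 2.8% and power of 59%, against 73% for ordinary errors.

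**The case against.** The strongest reply is that the article never states a common residual variance. It says linear regression, and the choice of standard error is commonly left to an analysis plan, which is not shown. That stands. The single variance is the default meaning of the stated method, not a written commitment, so this is no demonstrated error and the point is rated minor. It remains worth making because the article raises phenotype variability itself and answers it with an adjustment that acts on means only.

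A reader might infer that the error bars on every marker are wrong whenever spreads differ between conditions. The working shows otherwise: with equal marker spread the test keeps its level even under a threefold range of residual SDs. Resting EEG and MRI measures are not hand-based, so the design argument does not extend to them.

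A reader might also infer that the p-value tests zero association and equal variance jointly. It does not. The null is a zero slope, and unequal spread affects only the level of that test, under the joint condition described.

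Third, it is tempting to take as given that improvement varies more in the more disabled conditions. No passage says so, and floor effects could produce the opposite. Both the direction and the SD ratios are unknown. At a ratio of 1.25 the distortion is practically invisible.

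**Conclusion.** The point holds conditionally and is minor. If the pooled model is fitted with ordinary standard errors, and if a marker's spread and the residual spread vary together by condition, that marker's p-value and confidence interval are misstated. Over assumed SD ratios of 1.25 to 2 the type I error is about 5% to 12% when both are wider in the same conditions. In the reverse pattern at ratio 2 it is about 1%, with a loss of roughly 16 points of power (52% against 68% at a slope of 0.1). The SD ratios and the two-sided 5% level are assumptions. The slope estimates and the stated sample size are unaffected, and nothing here shows that any particular marker will be misjudged.

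**What to change.** Add one sentence to Statistical Analysis: in the pooled four-condition regressions, and in the pooled stroke-plus-spinal-cord-injury Fugl–Meyer regression, marker p-values and confidence intervals are based on HC3 standard errors. State that this does not apply to the 40-patient MRI subgroup model, where HC3 is conservative and costs power (59% against 73% in the case checked).

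The cost is a software option and about 1–2 points of power if spreads turn out equal. The model, its covariates and the sample size stay as they are.
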